## **4. RECRUITMENT**

The study team will inform the clinicians at the Adult Neurodevelopmental Services at CAMH and Surrey Place Centre about the study through an email introduction, followed by online meetings. Adult Neurodevelopmental Services, CAMH provide first-time intake psychiatric assessments to about 300 adults with IDD annually. 30% of them (around 90 people annually) may be potentially eligible patients. The treating physician/clinical care team will not obtain consent. They may identify potential research participants and obtain verbal permission from these potential participants and their SDM for a member of the research team to approach them. Potential participants and their substitute decision maker (SDM) who indicate further interest in hearing more about the study and provide assent to be contacted by a member of the research team will engage in an informed consent process (as described in the Telephone Screening Script).

CLEARR will be used to recruit participants for this study. CLEAR stands for Clinical Engagement And Research Recruitment. This has been approved by CAMH's Medical Advisory Committee, Information and Privacy Office and acknowledged by REB. All new referrals will be reviewed by the CLEAR coordinator and CLEAR physician for eligibility to participate using minimal inclusion/exclusion criteria outlined. Once a patient is identified, the attending physician will be notified via outlook calendar invite or email that their patient may be eligible for the study. The attending physician will decide whether research is appropriate for the patient and if so, they will ask the patient for consent to be contacted regarding the research study. If the patient provides verbal consent to be contacted to receive more information about the study, the physician will connect the patient with the CLEAR coordinator or study research team who will further explain the study. No PHI will be given to the study research team prior to the patient's consent.

Recruitment in the community (self-referral) will be conducted online via CAMH Research Registry, social media channels (Facebook, Twitter, LinkedIn, Instagram) and community organizations providing services for individuals with IDD and their families. Advertisements may also be posted on relevant Facebook and LinkedIn, or Instagram pages or be retweeted through their Twitter accounts. The message outlines the fundamentals of the study. Potential participants/SDM will then attend a research screening visit to determine eligibility if they meet all of the following criteria.

All potential participants and their SDM will be given the option to participate. Participation in the study is voluntary. The decision to participate will not affect patients' receipt of treatment or clinical services. Participants and their SDM will be informed that they have the option of terminating their participation at any time, without consequence and that no new data will be collected on them. Any existing data will be anonymized.

## **5. CONSENT**

- The research assistant will schedule the first appointment (research screening visit) to discuss the study and obtain written informed consent from the participant or their SDM.
  - The participant or their SDM will be provided with the informed consent form either by email, mail, or secure file transfer (as noted in the Telephone Contact Script) before the consent discussion.

- SDM consent is included as the patient may not have the capacity to make the decision about study participation. As per the Tri-Council Policy Statement: Ethical Conduct for Research Involving Humans, principle of respect for persons implies that those who lack the capacity to make decisions for themselves should have the opportunity to participate in research that may be of benefit to themselves or others. SDMs may decide whether participation in a particular study would be appropriate. These principles involve considerations of concern for welfare and justice.
- Consent will be documented on the written Informed Consent Form (ICF). This will include signatures from the participant/SDM, the person conducting the consent discussion, and the witness (if applicable). Full explanation about this study will be provided to the participants and/or their SDMs.
  - If the consent discussion is conducted in person, the participant/SDM will be provided with a completed and signed copy of the informed consent form at the end of their visit.
- The MacArthur Competence Assessment Tool for Clinical Research (MacCAT-CR) will be applied to both of them as needed in order to ensure that they understand the information presented in the ICF. A score of 70% or higher in the MacCAT-CR will be required to pass.
  - 1) If the participant passes the MacCAT, written informed consent will be obtained from the participant.
  - 2) If the participant is not able to complete or does not pass the MacCAT and their SDM passes the MacCAT, written informed consent will be obtained from the SDM.
- If the participant and their SDM choose to have the screening assessment and consent discussion virtually implemented (an elective process), they will receive the informed consent form either by email, mail, or secure file transfer (as noted in the Telephone Contact Script) before the consent discussion. If the participant/SDM chooses to receive the informed consent form by mail, after virtually conducting the consent discussion, we will document remote consent by acquiring a written signature from the prospective participant or their SDM on the paper informed consent form and have it mailed back to the research team using a pre-paid postage envelope. The research team member who conducted the consent discussion would then sign this informed consent form. Alternately, if the participant/SDM chooses to receive the informed consent form by email or secure file transfer, the participant/SDM will print and sign the informed consent form, and mail the completed form with their wet signatures back to the study team. If participants/SDMs choose to return the signed informed consent form by mail, we will provide a pre-paid postage envelope.
  - During videoconferencing/teleconferencing, we will assess capacity and address any questions raised by prospective participants/SDMs prior to documenting informed consent, as identical to a consent discussion conducted in person.

- The participant/SDM will receive a fully signed, complete copy of the informed consent form within 10 days following the informed consent process. This complete copy will be distributed by mail.
- The research procedures will only begin after the informed consent form signed by the participant/SDM (wet signature) is received and signed by the research team member who conducted the consent discussion.

## **6. STUDY DURATION**

The estimated length of time needed to complete the entire study is 2 years, including 3 months of start-up preparation, 18 months of participants recruitment and trials, and 3 months of data analysis and final reporting.

## **7. STOPPING OF THE STUDY**

### **7.1. Termination of the entire study**

Reasons for withdrawing individual participants from the study may include one or more of the following:

- a) Failure to continue to meet the inclusion criteria.
- b) Changes in participants' behaviours or situations, which meet the exclusion criteria. For example, participants become pregnant, newly use other cannabinoids, or newly use illegal psychomimetic substances as specified in Section 3.3, after the start of the trial.
- c) Major protocol violation.
- d) Participant lost to follow-up.
- e) Withdrawal of consent: Participation in the study is voluntary, and the participant can refuse or stop participation at any time. The participant's refusal to participate or withdraw from the study will not interfere in any way with the relationship with his/her doctor or hospital.
- f) Inability to tolerate the study medication or procedure.
- g) Serious adverse effects related to the study medication.
- h) New information shows that the study intervention is no longer in the participant's best interest.

In addition to these discontinuation criteria, any participant may be discontinued from the study at the discretion of the investigators if this is deemed to be in the best interest of the participant. The decision may be made either to protect the participant's health and safety, or because it is part of the research plan that people who develop certain conditions may not continue to participate. To ensure safety, we will arrange a Safety Follow-up visit, which is the same as the one for those who fully complete the trials, for participants withdrawn from the study.

Any research information recorded for, or resulting from, participation in this research study prior to the date that the participant formally withdraws from the study will be retained and may

continue to be used and disclosed by the investigators for research purposes. However, no new data will be further collected. There is no exception to the Safety Follow-up visit.

As the purpose of this phase I study is to investigate the tolerability of nabilone in adults with IDD, we will not recruit any new participants to replace the ones who withdraw from the entire trial.

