shipment inventory. Any damaged or unusable nabilone in a given pick-up will be documented in the clinical trial files. Regarding dispensing the study medication, participants/caregivers will come to CAMH at 3 separate times to pick up nabilone (Table 1), including 1) to pick up the package for the whole dose titration phase and the first 6 days of the stable dose phase at the Pre-treatment Visit (V 0), 2) to pick up the package for the remaining days of the stable phase, and 3) to pick up the package for the dose tapering phase at the Post-treatment Visit (V 1). Nabilone will be prepared for each visit by Research Pharmacy Service. Participants/caregivers will be requested to document the details of using nabilone and other concomitant medications in the drug diary. They will also be asked and expected to return the empty or any leftover nabilone back to the study team, to help with drug accountability.

Regular study intervention reconciliation will be performed to document nabilone assigned, consumed, and remaining. This reconciliation will be logged on a drug accountability log, and signed and dated by delegated research and/or pharmacy staff.

At the completion of the clinical trial, there will be a final reconciliation of the nabilone dispensed, consumed and remaining, based on the drug diary, the remaining drugs which are returned. This reconciliation will be logged on an accountability form, and signed and dated by delegated research and/or pharmacy staff. Any discrepancies noted will be investigated, resolved, and documented prior to return or destruction of unused study intervention. Intervention destroyed on site will be documented in the clinical trial's files.

All participants entering the dose titration phase will be included in the description of the safety profile and tolerability of nabilone (the Primary Objective). Participants completing the dose titration stage will be included in the final statistical analysis for the Exploratory Objective (i.e., explore changes in SBP in participants pre-and post-treatment), regardless of whether they complete the full protocol. This approach is consistent with the intention-to-treat principle.

**Figure 1.** A schematic diagram of the study procedures, including all study visits and timelines. Abbreviation: S-V: a screening visit; V 0: a baseline visit; V 1: a visit at the end of open label phase; V-F: a follow-up visit to ensure safety; d: days; wk: weeks; FU: follow-up; max: maximum.

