- Re-assessment of caregiver rated ABC-I, MOAS, General Anxiety Subscale of ADAMS. CGI-S and CGI-I will be rated by the investigator to evaluate the severity and improvement of the behavioural problems after nabilone treatment.
- Re-assessment of caregiver's stress and crisis using the Stress Subscale of DASS-21 and BFDS.
- Optional re-assessment of MRI Imaging for those who finish the pre-treatment MRI and are willing to receive the second wave of MRI imaging.
- Concomitant medication

Safety follow-up assessments include:

- Re-assessment of adverse events using the UKU side effect rating scale, examined by the researcher or investigator.
- Re-measuring of vital signs and weight.
- Concomitant medication
- Re-assessment of participants' cognitive capacity using the NIH Toolbox® Cognition Battery.
- Assessment of caregivers' acceptability of the study protocol using the custom-designed questionnaire, as completed by the caregiver.

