## **12. SAFETY MONITORING PLAN FOR ADVERSE EVENTS AND SEVERE ADVERSE EVENTS**

Adverse events (AEs) will be documented and reported as mandated by current regulations. AEs will be assessed at each study visit and telephone follow-up. All AEs, whether reported by the participant, SDM, or observed by study staff/investigators, will be recorded on the AE log along with a brief description, start date/resolution date and any action taken. The AE log will be initiated by the PI ([name]), who will make the determination on the relationship of the AE to the investigational drug/study procedures. All unexpected AEs determined by the PI to have a causal relationship with the investigational product or as a result of study procedures, will be reported to CAMH REB as part of the annual ethics approval renewal process. Where the event is deemed to meet CAMH REB reporting criteria, the PI will notify the REB. Every adverse event will be assessed and recorded in the participant's file by the PI or another physician involved in the study. The PI will report all Serious and Unexpected Adverse Drug Reactions (SUADR) to Health Canada as per Division 5 regulations.

If participants have AEs from participation in this study, medical care will be provided in the same way they would normally get medical care (for example, by going to their family doctor or seeking emergency medical treatment if needed). If participants withdraw from the study because they are unable to tolerate any AEs, or because of serious AEs, we will arrange a Safety Follow-up visit, which is the same as the one for those who fully complete the trials. If participants can tolerate the AEs, and the investigators consider that the continuation of participation in the study is still in the best interest of these participants, the frequency of the regular phone check-up during the open label phase will be increased from once weekly to once every two days to make sure these AEs do not progress to intolerable or more serious ones. In addition to intolerable AEs/severe AEs, there are other criteria which will remove participants from continuing the study (see Section 7.1).

Nonetheless, we do not have an independent Data and Safety Monitoring Board (DSMB) in the current trial for the following reasons:

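### Protocol Section 7.1 bars new data after any withdrawal, yet Sections 7.1 and 12 promise withdrawn participants a Safety Follow-up visit made up of safety assessments; whether those findings may be recorded and used is unresolved.

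*Protocol*

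**What the plan says.** **Section 7.1** lists eight reasons for withdrawing a participant, among them withdrawal of consent (e), inability to tolerate the drug or procedures (f) and serious adverse effects related to the drug (g). It makes three statements that apply to withdrawn participants without distinguishing these reasons:

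- On the visit: "To ensure safety, we will arrange a Safety Follow-up visit, which is the same as the one for those who fully complete the trials".
- On earlier data: information recorded "prior to the date that the participant formally withdraws from the study will be retained and may" still serve research.
- On later data: "However, no new data will be further collected. There is no exception to the Safety Follow-up visit".

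**Section 12** repeats the promise for exactly the group of most interest. For those who "withdraw from the study because they are unable to tolerate any AEs, or because of serious AEs, we will arrange a Safety Follow-up visit", again described as identical to the completers' visit.

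**Section 3.2 and Table 1** define that visit. It includes "Re-assessment of adverse events using the UKU side effect rating scale, examined by the researcher or investigator", plus vital signs, weight, concomitant medication, the NIH Toolbox and a caregiver acceptability questionnaire.

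**Section 4** tells participants that they may stop at any time "without consequence and that no new data will be collected on them". It makes no allowance for safety follow-up.

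**Section 3.1** places everyone who enters dose titration in the safety and tolerability description for the primary objective.

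**The concern.** A visit that consists of safety measurements is promised to people on whom no further data are to be gathered. Site staff cannot tell whether to record what they find at V-F, and an analyst cannot tell whether it belongs in the primary safety description.

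A bar on new data is natural for someone who withdraws consent to data collection. It does not fit someone taken off nabilone because of harm, who may be willing to be followed. Section 7.1 treats the two alike.

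What is at stake is safety information arising after withdrawal. Section 12 asks for a resolution date on the AE log, and that date may fall after the participant has left. This has to be settled in the protocol, because an analysis plan cannot recover data that the protocol told sites not to collect.

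**Working it through.** **1. The two readings of the last sentence in Section 7.1**

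| Reading | Consequence | Conflict |
|---|---|---|
| A. The data bar extends to V-F | The visit is held, but its findings are not collected | With the promise in 7.1 and Section 12 of the same visit as completers, which is made up of data collection |
| B. V-F is compulsory for all | V-F findings are collected | With the preceding sentence in 7.1, and with Section 4 for those who choose to stop |

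Neither reading leaves all the passages consistent.

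**2. What depends on V-F (Table 1, after the baseline visit V 0)**

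| Measure | Titration / open label | V 1 | V-F |
|---|---|---|---|
| AEs (UKU) | yes | yes | yes |
| Weight | no | yes | yes |
| Physical examination, vital signs | no | yes | yes |
| NIH Toolbox | no | yes | yes |

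For a participant who withdraws before V 1, V-F is the only scheduled post-dose value of weight, vital signs and cognition. UKU information from before withdrawal exists in any case; V-F adds the later course.

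**3. How many participants**

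Inputs: 40 entering titration and 25% attrition before the open-label phase (Section 8); 80% hypothesised to complete (Section 2).

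- The plan's own figure first: 40 × (1 − 0.25) = 30, as Section 8 states. Its detectable effect also reproduces: a paired t-test with n = 30, d = 0.53 and two-sided α = 0.05 has power 0.801. Neither figure is in dispute here.
- From attrition: 40 × 0.25 = 10 leave before the open-label phase, and hence before V 1.
- From the completion hypothesis: 40 × (1 − 0.80) = 8 do not complete.
- The two planning figures do not agree, since 25% attrition caps completion at 30/40 = 75%. Both are therefore kept as a range.
- The lower end is 0. The share stopping for AEs is not given, and Section 3.1 moves a participant with an intolerable AE in titration to the previous lower dose and on into the open-label phase, so such an event need not lead to withdrawal.

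Under reading A, between 0 and about 8 to 10 of 40 would lack V-F data; the upper end assumes that every non-completer formally withdraws. Under reading B the rule removes 0 of 40.

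**4. What that would mean for a finding seen only at V-F**

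With x participants showing the finding among those seen and w not seen, the share among all 40 lies between x/40 and (x + w)/40. The width is w/40: 8/40 = 20 percentage points, or 10/40 = 25. For an assumed x = 3, chosen only for illustration:

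- w = 8: 3/40 = 7.5% to 11/40 = 27.5%.
- w = 10: 3/40 = 7.5% to 13/40 = 32.5%.

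If no one seen has the finding, the one-sided 95% upper limit is 1 − 0.05^(1/n): 7.2% for n = 40, 8.9% for n = 32 and 9.5% for n = 30.

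These are upper-end cases under reading A, and they do not apply to AEs already recorded before withdrawal.

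**The case against.** The strongest reply is that the protocol's intention is plain. Sections 7.1 and 12 both undertake to hold a full safety visit, and the disputed sentence reads at least as naturally as making that visit compulsory. On that view nothing is lost and only the wording is poor. The bar can also be read as aimed at participants who choose to leave, because the retention sentence is tied to formal withdrawal and Section 4 concerns voluntary termination.

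Further, the event that led to stopping is kept. AEs are checked every two days in titration, and Section 8 summarises safety as the percentage with each adverse effect, so that event is already counted. Some non-completers, such as those lost to follow-up (d), would supply no V-F data under any wording.

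Most of this stands, and it limits the size of the point. It does not remove the conflict. The bar follows a list that includes intolerance and serious adverse effects and is not confined to consent withdrawal. Reading the visit as compulsory still leaves it at odds with the sentence before it and with Section 4.

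A reader might go further and infer that those who stop for AEs contribute no follow-up safety data, or that the safety profile is therefore biased in nabilone's favour. The documents support neither. The first takes reading A as settled. The second needs event rates after withdrawal, which the protocol does not give.

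**Conclusion.** The point holds as an internal contradiction on a matter that bears on the primary objective. The protocol does not settle whether safety data from the V-F of withdrawn participants are collected and used, and it does not separate stopping treatment from withdrawing consent to data collection.

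The possible loss is confined to information after withdrawal and is conditional on the bar covering V-F. The number who would be affected because they stopped for AEs cannot be derived from the protocol, and no direction of bias is established. The clearest exposure is a participant who leaves before V 1 and would then have no scheduled post-dose weight, vital signs or cognitive result.

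**What to change.** Reconcile Sections 4, 7.1 and 12:

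- In Section 7.1, distinguish participants who stop nabilone or are withdrawn for reasons other than withdrawal of consent from those who withdraw consent to further data collection.
- For the first group, state that the V-F safety measures already planned (UKU, vital signs, weight, concomitant medication, NIH Toolbox), and AE outcomes known by that visit, are recorded and included in the primary safety description as far as they can be obtained. Acknowledge that this will not be possible for those lost to follow-up, and that Section 7.2 already excuses participants who cannot do the NIH Toolbox.
- Limit the bar on new data to the second group, and replace the ambiguous last sentence with one that says which rule applies to V-F.
- Bring Section 4 and Section 12 into line. The consent form was not available for this review; check that it says the same.

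The cost is a wording amendment, with a consent change only if that check shows one is needed. No new visit or assessment is required, because V-F is already promised to withdrawn participants.

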## **7.2. Stopping of parts of the study**

If participants fail to discontinue the use of any cannabinoids or high doses of benzodiazepine (more than the benzodiazepine equivalent to lorazepam 2 mg daily), psychostimulants for attention-deficit hyperactivity disorder (ADHD), and nonbenzodiazepine hypnotics 4 weeks before the start of the titration phase, they will not progress to the Pre-Treatment visit (V 0). We will discuss with participants and their caregivers to confirm their willingness to further proceed with the study. The participants are only permitted to proceed with the trial when they do not fulfill this exclusion criterion of the concurrent use of other cannabinoids and high dose of benzodiazepine.

If participants cannot, or are unwilling to, comply with the procedures of NIH Toolbox® Cognition Battery, but can comply with the remaining parts of the study, we will stop assessing them using this cognitive battery. These participants will still proceed with the other parts of the entire studies.

